## Abstract

**Background:**

Oral anticoagulation prevents strokes in patients with atrial fibrillation but, for reasons that remain unclear, less than 40% of all patients with atrial fibrillation receive warfarin. The literature postulates that patient and clinician preferences may explain this low utilization.

**Design:**

The proposed research seeks to answer the following questions: i) When assessed systematically, do patients' and clinicians' preferences explain the utilization of warfarin to prevent strokes associated with atrial fibrillation? ii) To what extent do patients' and clinicians' treatment preferences differ? iii) What factors explain any differences that exist in treatment preferences between patients and clinicians? To answer these questions we will conduct a two-phase study of patient and clinician preferences for health states and treatments. In the first phase of this study we will conduct structured interviews to determine their treatment preferences for warfarin vs. aspirin to prevent strokes associated with atrial fibrillation using the probability trade-off technique. In the same interview, we will conduct preference-elicitation exercises using the feeling thermometer to identify the utilities that patients place on taking medication (warfarin and aspirin), and on having a mild stroke, a severe stroke, and a major bleed. In the second phase of the study we will convene focus groups of clinicians and patients to explore their answers to the exercises in the first phase.

**Discussion:**

This is a study of patient and clinician preferences for health states and treatments. Because of its clinical importance and our previous work in this area, we will conduct our study in the clinical context of the decision to use antithrombotic agents to reduce the risk of stroke in patients with non-valvular chronic atrial fibrillation

## Background

Chronic atrial fibrillation (AF) is the commonest sustained cardiac arrhythmia. The prevalence of AF increases from less than 1% in patients younger than 60 years to almost 10% in patients over the age of 80 years [1,2]. Similarly, the incidence of AF increases from 0.2% per year in men under the age of 40 years to more than 2% per year in men aged 80–89 years, with a lower age-adjusted incidence in women [3]. This condition is associated with substantial mortality and morbidity from stroke, thromboembolism and heart failure [4]. On average, 5 out of every 100 patients will have a stroke every year of whom 3 will have severe disability or die prematurely [5,6]. Warfarin reduces the risk of strokes by 65% [7].

A recent systematic review of practice surveys found that 56 to 85% of patients with atrial fibrillation are not receiving warfarin [8]. As a result thousands of these patients will suffer preventable strokes every year and many will be left with severe and permanent disability or will die prematurely. Why do these patients and their clinicians choose not to use warfarin? Although this review identifies some system barriers to anticoagulation [8], the most common reason for not offering and prescribing warfarin to patients with atrial fibrillation was clinicians' perception that patients were at high risk of bleeding [9]. This point suggests that clinicians must consider the majority of patients with atrial fibrillation to be at sufficiently high risk of bleeding to warrant withholding warfarin. This behavior is consistent with clinicians being more bleeding-averse than stroke-averse. The catastrophic impact of major stroke on patients' lives raises questions about these apparent values. The wisdom of withholding anticoagulation is further challenged by data suggesting that clinicians' ability to assess their patients' risk of bleeding on warfarin is no better than chance [10].

One needs to weigh the benefits of stroke prevention against the inconvenience and cost of taking warfarin daily, the inconvenience of periodic blood testing to monitor anticoagulation, and the risk of both minor and major bleeding. In addition, there are alternatives to warfarin. Aspirin is less effective than warfarin in avoiding strokes, it is less likely to cause bleeding [11], and requires no laboratory testing to monitor its effects. If patients choose not to take either warfarin or aspirin, they minimize their risk of bleeding and the inconvenience of using these treatments, but are left with an increased risk of stroke.

Perhaps patients and clinicians do not choose to use warfarin because they prefer to avoid the risk of bleeding associated with its use. This perspective may be particularly true for those patients considered at high risk of bleeding. In this proposal, we will describe a prior study we conducted that suggests that this explanation is unlikely [12]. Our results suggested that patients were much more stroke-averse than bleeding-averse (Figure 1). On the other hand, clinicians were less stroke-averse and more bleeding-averse than the patients. If these results are accurate and widely generalizable, they suggest that warfarin is underutilized and that the utilization rates are not consistent with patient values but are determined by physician values. Another way to look at the results involves determining what participants implied about the relative values of strokes and bleeds. In effect, clinicians' felt that the adverse consequences of a severe gastrointestinal hemorrhage had more or less the same value (or disutility) as the adverse consequences of a stroke. This was in spite of describing that half of the strokes were severe enough to lead to irreversible major disability or death and of describing severe gastrointestinal bleeds as transitory events associated with transfusions, endoscopy, and relatively rapid recovery to pre-morbid function.

**Figure 1 F1:**
[figure not shown]
**Bleeding thresholds for warfarin**[12]

If our findings were valid (i.e., they truly reflect individual patient and clinician choices) and generalizable, they would have profound implications. First, they suggest that current clinician behavior of withholding warfarin in patients at risk of bleeding is inconsistent with the values and preferences of patients. Second, if clinicians were to behave in a way consistent with patient preferences, patients would likely experience fewer strokes thanks to wider warfarin use. Thus, if confirmed, our findings will call for interventions to align clinician behavior with patient preferences.

It is possible, however, that other considerations may explain our previous findings. First, our previous study lacked an optimally detailed presentation of warfarin use. To varying degrees, most decision analyses on the choice of antithrombotic therapy for atrial fibrillation are sensitive to patients utility for the inconvenience associated with warfarin administration [13-17], which has been as low as 0.92 on a 0 to 1.0 scale where 0 is death, and 1.0 full health [18]. Failure to present all the inconveniences of warfarin use in vivid detail ("unpacked" and described in its many components) could lead to an underestimation of its relative importance [19].

Second, we did not include consideration of deaths from all cause and those resulting from bleeding. The literature does not emphasize the 20% reduction in the risk of dying associated with warfarin when compared to placebo [7]. There are fewer deaths (although this difference does not reach statistical significance) among patients using warfarin than among patients using aspirin [11]. However, as the bleeding risk increases with warfarin (as we will model during the probability trade-off exercise) the number of deaths due to bleeding (at most, 10% of severe gastrointestinal bleeds will die) will also increase and eventually offset the small probable mortality benefit of warfarin over aspirin. We instructed clinicians and patients to consider the scenarios as presented, ignoring other issues that might come into play in other situation. It is possible, however, that while patients were easily able to follow these instructions, clinicians incorporated their knowledge of issues of inconvenience of warfarin use and of bleeding deaths in their evaluation.

Limitations of our prior study, however, permit alternative explanations of our findings. In particular, we did not highlight for patients the inconvenience of warfarin therapy, the risk of death with bleeding, nor the risk of death with strokes. Discrepancies in clinician and patient responses may be explained by clinicians taking these factors into account, while patients did not. The goal of this proposal is to resolve uncertainty in the interpretation of our prior study, and deepen our understanding of how clinicians make decisions about warfarin use in patients with atrial fibrillation. The implications of the study proposed are potentially profound: if differences in clinician and patient values and preferences underlie the current apparent underutilization of warfarin, it can be inferred that there are truly hundreds of thousands of patients experiencing an unnecessary devastating stroke each year. Such a result will mandate the development and testing of interventions to align clinician behavior with patient preferences.

## Design

The proposed research seeks to answer the following questions:

1) When assessed systematically, do patients' and clinicians' preferences explain the utilization of warfarin to prevent strokes associated with atrial fibrillation?

2) To what extent do patients' and clinicians' treatment preferences differ?

3) What explains any differences in treatment preferences between patients and clinicians?

To answer these questions we will conduct a two-phase study of patient and clinician preferences for health states and treatments. In the first phase of this study we will conduct structured interviews with patients and clinicians to determine their treatment preferences for warfarin vs. aspirin treatment to prevent strokes associated with atrial fibrillation. In the second phase of the study we will convene focus groups of patients and clinicians to explore their answers to the exercises in the first phase. The ethics committee of the Hospital Sant Pau (Barcelona, Spain) approved the study.

### Setting and target population

#### Setting

We will conduct this study at three cities in Spain (Barcelona, La Coruña and San Sebastian). For each site several hospitals will collaborate to recruit the required number of cardiologists and internists. For the recruitment of general practicioners we will recruit from the Primary Health Care areas that belong to these hospitals in each of the three cities. This multicenter approach will limit the influence of local views about treatment of atrial fibrillation on the results of our study and will increase generalizability.

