#### Recruitment strategy

We will use several strategies to recruit patients and clinicians for this study. In the case of patients we will sample them from the different databases of the Health Areas from the three sites where the study will take place. Each site will provide a random sample of patients fulfilling eligibility criteria for participation. We will invite these patients to participate initially with a phonecall from their primary care physician or a delegate from their center. The study coordinator will follow-up with a phone call to verify eligibility, obtain verbal consent, and set up an interview date. Patients will give written informed consent to participate.

We will sample practicing clinicians working in general medicine (primary care, family medicine, internal medicine) and in cardiology, based in the community or in the hospitals. Clinicians who spend less than 30% of their time seeing patients in the outpatient or inpatient settings or if they have not cared for a patient with atrial fibrillation in the preceding six months are ineligible to participate. These eligibility and exclusion criteria should select clinicians who participate in making decisions about antithrombotic therapy with patients with atrial fibrillation, the most relevant group for our study. We will send an electronic letter to clinicians inviting them to participate in this study. A second mailing will follow if the local investigator receives no answer. Finally, clinicians who have not responded to the 2 mailings will receive a phone call from the local study investigator (a local colleague) inviting them to enroll.

In our experience, time is the main barrier to clinician participation. We plan to complete each clinician interview within 30 minutes. To achieve this goal, we will use a highly scripted interview with extreme economy of items. To ensure the success of the focus groups, we will use multiple ways to get clinicians to the focus group venue on time. These include, but are not limited to, sending periodic e-mail reminders, contacting their administrative assistants to include the focus group on their daily calendars, making same-day reminder phone calls, and arranging for transportation to the focus group venue, as needed.

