##### Differences in treatment preferences between patients and clinicians

We will test the difference of the means of *b *between the patients (*b*_*p*_) and clinicians (*b*_*c*_) using an unpaired *t *test. The observed distribution of *b*_*p *_in our preliminary work was highly skewed. This was because patients clustered at the highest *b *offered. For this study, we propose to offer a maximum *b *that is twice as large as the maximum *b *offered in our preliminary study. Furthermore, we will be studying a relatively large number of patients and clinicians with distribution of the means approximating the normal distribution with SEM = SD/vn. Our sample sizes will be considerably larger than 30, a size which is often taken as a guideline threshold, above which the sample distribution of the sample mean will be reasonably normally distributed, even if the distribution of individual values is substantially skewed. Thus, the use of the t-test is appropriate. However, we will also use the Mann-Whitney test, a non-parametric test that does not require the assumption of normality of the distribution. After identifying pertinent subgroups in the analysis to Research Question 1, we will conduct modified *t *tests to test the difference of the means of *b *between the patients and the subgroup of clinicians of interest. A modified *t *test is based on the pooled estimate of variance from all the subgroups [33]. The resulting *P *values can be adjusted for multiple comparisons using the Bonferroni method (multiplying the resulting *P *value by the number of paired comparisons performed).

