##### Sample size estimation

We require six focus groups, 1 of generalists and 2 of cardiologists at Barcelona, 1 of generalist at Galicia and País Vasco. We will undertake 1 group of patiens in each site. Ideally, each group should have 8 to 10 participants. We anticipate that not every clinician will be able to participate. To ensure 8 clinicians per group, we will enroll 12 potential participants per group. We will construct the focus groups to maximize homogeneity of specialty, experience with patients with atrial fibrillation, and treatment preferences during individual interviews (phase 1). From our survey of faculty at the 3 sites, less than 10% of clinicians at each site are not eligible. Therefore we would need to enroll 20% of eligible clinicians at each site to achieve our sample size of 96 clinicians which will ensure adequate numbers for the focus groups.

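### The plan neither fixes matching site shares for patients and clinicians nor adjusts their comparison for site, so site could confound the contrast if the mixes differ

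*Protocol article*

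**What the plan says.** - **Setting** names three cities and gives a reason for using several: "This multicenter approach will limit the influence of local views about treatment of atrial fibrillation on the results of our study".
- **Recruitment strategy** covers patients: "Each site will provide a random sample of patients fulfilling eligibility criteria for participation". It sets no number per site.
- **Sample size estimation** covers clinicians: "we would need to enroll 20% of eligible clinicians at each site to achieve our sample size of 96 clinicians". It gives no count of eligible clinicians by site. The totals are 96 patients and 96 clinicians.
- **Sample size estimation** also lists the phase 2 clinician focus groups as "1 of generalists and 2 of cardiologists at Barcelona, 1 of generalist at Galicia and País Vasco", and for patients says "We will undertake 1 group of patiens in each site".
- **Differences in treatment preferences between patients and clinicians** sets the main comparison: "We will test the difference of the means of" b in the two groups by unpaired t test, with a Mann-Whitney test alongside. The proportions choosing warfarin at b_RCT are compared by Fisher's exact test with an exact interval for the odds ratio.
- **Differences in utilities between patients and clinicians** uses Mann-Whitney and t tests.
- **Description of treatment preferences** is the only place where site enters the analysis: the distribution of b is described by site in both groups. The exploratory regression in that section uses clinician characteristics and guides the choice of subgroups. It does not adjust the patient-clinician test.

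**The concern.** Patients and clinicians are not randomised to their groups, so anything that affects b and is spread differently over the two groups becomes part of the estimated difference. The authors themselves expect local views on treatment to matter. Recruiting in several cities dilutes the views of any one city in the overall averages. It protects the contrast between groups only if both groups have the same site mix or the analysis conditions on site. The plan secures neither.

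The Discussion would read a patient-clinician difference as grounds for urgent work to raise anticoagulation rates, and similar choices as a sign that current rates are appropriate. Confounding by site could push the result either way: it can create a difference or mask one. The subgroup tests, which compare selected clinicians with all patients, would be exposed in the same way.

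**Working it through.** **The plan's own figure.** With 96 per group and two-sided alpha 0.05, the standard error in SD units is √(1/96 + 1/96) = 0.1443. For a difference of 0.4 SD, 0.4/0.1443 = 2.771, and power is Φ(2.771 − 1.960) = Φ(0.811) = 0.791 (0.787 with the noncentral t). Table 2 gives .79, so it reproduces. The calculation contains no site component.

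**Inputs for the site check**
- From the article: 96 per group and three sites.
- Not in the article: site shares of the interviewed participants, and any difference in b between sites. Both are assumed below over a range.
- The largest imbalance tried is Barcelona with 60% of clinicians (3 of 5 focus groups, reading the Galicia and País Vasco phrase as one group each) and 33% of patients (1 of 3 groups). This borrows a phase 2 layout for illustration; it is not a stated phase 1 split.

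**Formulas.** Let D be the gap in mean b between Barcelona and the other two sites, in within-site SDs, and let p_c and p_p be the Barcelona shares of clinicians and patients. Assume no patient-clinician difference within any site.
- Bias = (p_c − p_p) × D.
- SE = √{[1 + p_c(1 − p_c)D²]/96 + [1 + p_p(1 − p_p)D²]/96}, which includes the spread that the site gap adds within each group.
- With s = bias/SE, rejection rate = Φ(s − 1.96) + Φ(−s − 1.96).

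Example, 60% against 33% and D = 0.8: bias = 0.267 × 0.8 = 0.213. SE = √(1.1536/96 + 1.1422/96) = 0.1546, so s = 1.38 and the rejection rate is 0.281.

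| Barcelona share, clinicians v patients | D = 0.3 | D = 0.5 | D = 0.8 |
|---|---|---|---|
| 60% v 33%: bias (SD) | 0.08 | 0.13 | 0.21 |
| 60% v 33%: rejection rate | 8.5% | 14.6% | 28.1% |
| 45% v 33%: bias (SD) | 0.035 | 0.058 | 0.093 |
| 45% v 33%: rejection rate | 5.7% | 6.8% | 9.3% |
| Equal shares: bias (SD) | 0 | 0 | 0 |
| Equal shares: rejection rate | 5% | 5% | 5% |

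Under the 60% v 33% split, a bias as large as the 0.4 SD target would need D = 0.4/0.267 = 1.5 SD.

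**Cost of adjusting, under the 60/20/20 v 33/33/33 split.** Clinicians per site are 57.6, 19.2 and 19.2; patients are 32 at each. The within-site information is the sum of n_c·n_p/(n_c + n_p) = 20.57 + 12 + 12 = 44.57, so the variance is 1/44.57 = 0.02244, against 2/96 = 0.02083 unadjusted. The ratio is 1.077. Power at 0.4 SD becomes Φ(0.4/√0.02244 − 1.960) = Φ(0.71) = 0.76. With equal shares the ratio is 1.

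**The case against.** The strongest reply is that the article never shows the site mixes to differ, and confounding needs both unequal mixes and a site difference in b. That is right. A reader might infer from the focus-group list that clinicians and patients are drawn in different site proportions, but the documents do not support it:
- The list concerns phase 2, and it does not fit the rest of the article. Setting and participants (second phase) plans three clinician and three patient groups, which is compatible with one of each per site. Sample size estimation says six groups but, on the natural reading, lists five for clinicians plus three for patients.
- Five groups with 12 clinicians enrolled for each make 60, not 96, so the list does not determine the mix of the 96.
- The 20% per site can be read as a feasibility check. Even as a rule, it shows no imbalance, because patient numbers per site are open and could match.

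Three further points have force. Setting claims only that several sites will limit local influence, which is a modest claim. Describing b by site would reveal a large gap. And the earlier study's difference was 0.9 with SDs of 0.9 and 0.8, or 0.9/√[(0.81 + 0.64)/2] = 1.06 SD; a bias of 0.08 to 0.21 SD would not overturn an effect of that size.

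What remains is that the article names its tests, and none conditions on site. A description by site does not correct the estimate or its P value. The study is also powered for 0.4 SD, where a bias of this size would count. An unsettled mix is a reason to adjust; it is not evidence of balance.

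**Conclusion.** The point holds as a conditional one. Matching site shares are not fixed, and the comparisons of b, of the proportion at b_RCT and of utilities carry no site term, so the protection that Setting attributes to three cities is not secured by the analysis. The size cannot be known from the article. Under the illustrative 60% v 33% split, the bias is 0.08 to 0.21 SD for site gaps of 0.3 to 0.8 SD, at most about half of the 0.4 SD target, with a false-positive rate of about 8.5% to 28%. Under 45% v 33% the rate stays below 10% over the same gaps, and under equal mixes there is no bias. It would be wrong to report that the study is confounded by site or that its site mixes are unequal. The point is worth acting on because the remedy is cheap and uses a variable that is already available.

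**What to change.** - Test the difference in b in a linear model with group (patient or clinician) and site (three levels), and report the group coefficient with its 95% confidence interval.
- Replace the plain Mann-Whitney test with its site-stratified form (van Elteren).
- Estimate the b_RCT odds ratio stratified by site.
- Treat the utility comparisons in the same way.
- Keep the unadjusted tests as supportive, and report the numbers of patients and clinicians by site.

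Recruiting equal numbers of patients and clinicians within each site would remove the imbalance at source, if still feasible.

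The analysis change needs wording only, since b is already to be described by site. It costs 2 degrees of freedom out of 190 and, under the 60/20/20 clinician split, about 7.7% more variance (power at 0.4 SD from 0.79 to about 0.76). If the mixes turn out equal, almost nothing is lost.
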